### Intervention

Participants are randomised to receive either perindopril 4 mg once daily or matching placebo, and to receive leucine 2.5 g three times per day or matching placebo. The perindopril/placebo is administered as oral capsules. Placebo and active capsules are identical in external appearance. Perindopril tablets are over-encapsulated with a hard gelatin capsule and backfilled with lactose. The placebo capsules are identical in appearance and packed with lactose. The starting dose of perindopril is 2 mg daily which is up-titrated to 4 mg after 2 weeks if tolerated and renal function, serum potassium levels and blood pressure remain within defined limits (potassium < 5.0 mmol/L, creatinine < 180 μmol/L and < 30 μmol/L rise from baseline, systolic blood pressure > 90 mmHg). Participants in the placebo group also undergo a ‘mock’ up-titration. If the 4 mg daily dose is not tolerated, participants are down-titrated to the original 2 mg daily. If 2 mg is also not tolerated, medication is withdrawn.

The leucine/placebo is administered as a powder. A 1.5-ml scoop is provided and participants are instructed to take three scoops (4.5 ml equivalent to 2.5 g of leucine/placebo) three times per day. The placebo is matching lactose powder. Participants are instructed that they should mix the powder with food or drink. Exploratory work with our local Older People’s Advisory Group indicated that mixing the leucine powder with food or drink was palatable, particularly if mixed with foods such as yoghurt or orange juice.

Randomisation is conducted via a centrally controlled, web-based Good Clinical Practice-compliant randomisation system, run by Tayside Clinical Trials Unit. Investigators at each site access the web-based system to randomise each participant at the end of the baseline visit. Randomisation is stratified by site. To ensure balanced assignment across critical variables, a minimisation algorithm is employed, using baseline age (> 80 vs ≤ 80 years), sex, SPPB score (> 8 vs ≤ 8), grip strength (> 25 vs ≤ 25 kg for males; > 15 vs ≤ 15 kg for females) and Charlson co-morbidity score (> 3 vs ≤ 3) to balance allocation across trial arms.

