Participants are asked to return all unused study medication including empty bottles/containers. Adherence to medication will be recorded by capsule count of the perindopril/placebo capsules and by the weight of the container for the leucine/placebo powder. Serum angiotensin converting enzyme (ACE) is measured to assess adherence to the perindopril/placebo capsules. To ensure that medication adherence is maximised, we employ a combination of written information about the study medication and why taking it is important, together with aide memoirs including LACE-branded mugs and fridge magnets. At each visit, participants are reminded about the importance of medication adherence. Interventions incorporating these components have been shown in a Cochrane review to enhance adherence [31]. If one of the study drugs needs to be stopped or the participant wishes to stop, they are encouraged to continue with the other study drug. Participants stopping both study drugs are encouraged to remain in the study in order to facilitate analysis as randomised.

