**Fig. 2 Fig2:**
[figure not shown]
SPIRIT diagram for the LACE trial. 6MWD six minute walking distance, ACE angiotensin converting enzyme, BIA bioimpedance analysis, DXA dual-energy X-ray absorptiometry, eGFR estimated glomerular filtration rate, EQ5D EuroQol 5D, FFQ Food Frequency Questionnaire, IMP investigational medicinal product, NEADL Nottingham Extended Activities of Daily Living, SPPB Short Physical Performance Battery

In addition, we are collecting data on adverse events, falls, hospitalisation, death and admission to institutional care. Consent is obtained for open-label follow up of participants for these outcomes collected from routine clinical data following the end of the 1-year study period. We are collecting data on usual physical activity and diet at baseline and 12 months using step counts measured by an OMRON pedometer and the Scottish Collaborative Group Food Frequency Questionnaire (FFQ) respectively; this will allow the interaction between treatment and protein intake (total, plant vs animal protein) to be ascertained.

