### Statistical analysis

Analyses will be by group as randomised and will comply with the International Conference on Harmonisation (ICH) E9 ‘Statistical Principles for Clinical Trials’ [35]. Two-sided *p* < 0.05 will be taken as significant for all analyses. The primary analysis will be a repeated-measures, mixed-model between-group comparison of SPPB utilising all available data points during follow up. Initially, a test for treatment interaction between perindopril and leucine will be carried out and if not significant the main analysis will proceed using the full power of the factorial design; each intervention will be assessed separately as an independent hypothesis. Treatment effect estimates for all primary and secondary outcomes will be adjusted for baseline values, age, sex and minimisation variables.

Secondary outcomes will be analysed with similar methodology using repeated-measures, mixed-model, between-group comparisons. Unadjusted and adjusted analyses will be presented as already discussed. Sensitivity analyses will be performed to further test the effect of missing data both by multiple imputation and by assigning worst-possible result status to missing data points. A supplementary per-protocol analysis will be performed to examine adverse events in those taking at least 80% of their study medication.

No interim analyses are planned. Exploratory sub-group analyses will be performed, including examining differences in treatment effects by age (above and below median), SPPB (> 8 vs ≤ 8) and sex. A full Statistical Analysis Plan will be prepared and finalised prior to trial database lock, and will be made available as an additional upload on the *Trials* website once finalised.

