### Trial oversight and monitoring

Trial oversight is provided by an independent Trial Steering Committee (TSC), which meets at least every 6 months. Members include academic geriatricians with trials experience and three lay members, together with the chief investigator. The TSC reviews trial progress, approves any significant protocol changes, advises on trial conduct and approves analysis plans and dissemination plans. The TSC reports to the funder (NIHR), who has final decision-making authority for the trial. An independent Data Monitoring Committee (DMC) meets at least every 6 months; this committee comprises three independent members, chaired by an academic geriatrician with trials experience, and contains a minimum of one independent statistician. The DMC reviews trial adverse events and safety data, and makes recommendations to the TSC. Charters for conduct of the TSC and the DMC are available from the study team and from the funder. Routine management of the trial is provided by the Trial Management Group (TMG), which comprises the grant co-applicants, local site investigators, trials unit personnel from project management, data management and statistics teams, Sponsor representatives and Sponsor monitors.

Monitoring of the trial conduct at each site is provided by the Sponsor. Monitoring takes place according to a pre-specified plan, with site visits conducted according to the recruitment rate and frequency of problems identified by remote monitoring of study data. Both the Sponsor and the Clinical Trials Unit are subject to periodic audit by the UK Medicines and Healthcare products Regulatory Agency. The funder provides monitoring of overall trial progress, with additional input from the independent TSC. The final decision to publish lies with the funder (NIHR) and the Sponsor; the funder and the Sponsor have both reviewed the study design. The Sponsor will have no input into data collection, analysis and interpretation; the final report will be peer reviewed by the Funder prior to finalisation.

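### The supplementary adverse-event analysis in participants taking at least 80% of medication selects on a consequence of harm and will tend to understate absolute excess risk for events that lead to stopping

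*Protocol article*

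**What the plan says.** The Statistical analysis section of the protocol article opens with the general principle: "Analyses will be by group as randomised". After the sensitivity analyses for missing data it adds: "A supplementary per-protocol analysis will be performed to examine adverse events in those taking at least 80% of their study medication". This is the only analysis of adverse events that the article names, and the only use it gives to a per-protocol set.

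The Intervention section describes how participants come off drug. Someone who does not tolerate the higher perindopril/placebo dose steps down, and then: "If 2 mg is also not tolerated, medication is withdrawn". Where one drug has to stop or the participant wishes to stop it, "they are encouraged to continue with the other study drug". On follow-up: "Participants stopping both study drugs are encouraged to remain in the study in order to facilitate analysis as randomised". Adherence is measured separately for each product: "Adherence to medication will be recorded by capsule count of the perindopril/placebo capsules", and container weight is used for the powder.

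Adverse-event collection and review carry no adherence restriction. Under Outcomes, beside the SPIRIT figure, the article says "we are collecting data on adverse events, falls, hospitalisation, death and admission to institutional care". Under Trial oversight and monitoring it says "The DMC reviews trial adverse events and safety data, and makes recommendations to the TSC".

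**The concern.** Reaching 80% adherence happens after randomisation and can be prevented by the events being counted. A participant who has an adverse event, cannot tolerate the capsules and is taken off them may fall below 80% and so leave the set in which adverse events are examined. Those who remain are, in part, those who tolerated treatment. Where a drug causes an event that leads to stopping, the arm with more such events loses more of them, and the absolute difference between arms shrinks.

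This matters for reading the results. A reader will take a table of harms in adherent participants as showing harm under good exposure. If it shows a smaller absolute excess than the as-randomised table, it may be read as reassurance, in a trial of people aged 70 and over. The article does not warn against that reading.

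The factorial design adds a practical difficulty. A participant may stop the capsules because of harm and continue the powder. Whether that person belongs in the perindopril comparison depends on which product the 80% refers to.

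**Working it through.** **The plan's figures.** The protocol states no adverse-event rate, stopping rate or safety power, so there is no figure to reproduce on this point. The sample size rests on the SPPB and muscle mass and has no bearing here.

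**Step 1: who can leave the set.** The article gives no denominator for the 80%. If it is the planned year, 0.80 × 365 = 292 days. Anyone who stops before about day 292 is then out, including anyone withdrawn for intolerance during titration. If the denominator is time on drug, an early stopper could remain. Late stoppers can reach 80% under either reading.

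**Step 2: a simple selection model (all inputs assumed).** Let p be the true event risk and q the share of participants with the event who fall below 80% because of it. Non-adherence for unrelated reasons, if equally likely with and without the event, cancels. The risk in the 80% set is

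p(1 − q) / [p(1 − q) + (1 − p)].

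Take true risks of 15% v 5%: difference 10 points, ratio 3.0.

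- q = 0.5: 0.075/(0.075 + 0.85) = 8.1% and 0.025/(0.025 + 0.95) = 2.6%. Difference 5.5 points, ratio about 3.16.
- q = 0.7: 0.045/(0.045 + 0.85) = 5.0% and 0.015/(0.015 + 0.95) = 1.6%. Difference 3.5 points, ratio about 3.23.

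So 45% to 65% of the absolute excess disappears, while the ratio rises slightly.

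**Step 3: a wider range.** Assume control risks of 10% or 20%, q of 25%, 50% or 75%, and 10% unrelated non-adherence among those without the event. The risk in the set is then p(1 − q)/[p(1 − q) + 0.9(1 − p)].

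| True excess (points) | Excess in the 80% set (points) |
|---|---|
| 5 | 1.7 to 4.5 |
| 10 | 3.5 to 9.1 |
| 15 | 5.5 to 13.7 |

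For example, with a control risk of 10% and a true excess of 10 points, the excess in the set is 8.8, 6.4 and 3.5 points for the three values of q. The ratio goes from 2.0 to between 2.03 and 2.17.

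**Step 4: stopping that depends on cause.** Steps 2 and 3 assume that an event is equally likely to end treatment in both arms. Suppose instead that 70% of drug-caused events and 25% of background events take the participant below 80%, with true risks of 15% v 5% (5 points background, 10 points drug-caused).

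- Active: events kept = 0.05 × 0.75 + 0.10 × 0.30 = 0.0675; risk = 0.0675/(0.0675 + 0.85) = 7.4%.
- Control: events kept = 0.05 × 0.75 = 0.0375; risk = 0.0375/(0.0375 + 0.95) = 3.8%.

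The difference falls to 3.6 points and the ratio from 3.0 to 1.9. Whether relative harm is also understated depends on this assumption.

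**Step 5: a case in the other direction.** Suppose nobody stops because of harm, 10% are non-adherent for unrelated reasons and have no drug effect, and adherers have a 10-point effect. The as-randomised difference is 0.9 × 10 = 9 points, and the difference in the 80% set is 10. Restriction then raises the difference.

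**The case against.** The strongest reply is that the analysis is labelled supplementary and sits under an as-randomised principle. Those who stop both drugs are encouraged to stay in the study, and adverse events are collected and reviewed by the Data Monitoring Committee whatever the adherence. A secondary table cannot remove events from the as-randomised comparison. This stands. A reader might infer that the trial's safety conclusion is biased toward no difference; the document does not support that.

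Other parts of the reply also stand:

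- Intolerance leads first to a step down, so not everyone with intolerance comes off the capsules. The withdrawal rule concerns the capsules only. It is tempting to say that those removed come mostly from the active perindopril arm, but no figure supports it.
- A condensed article may leave the 80% denominator and its application to each product to the analysis plan, which is not shown. It is also tempting to say that the rule pools the two drugs. The article measures adherence separately and assesses each intervention separately, so one phrase about study medication does not establish pooling.
- Every rate above is assumed, and under equal stopping in both arms the risk ratio is not reduced.

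What the reply does not remove is the choice itself. The article fixes an adherence-restricted set for examining harm and names no other adverse-event analysis. Its own withdrawal rule links leaving that set to harm. A fuller analysis plan could define the threshold more closely, but that would not stop the set from depending on tolerance. The reversal in Step 5 needs little or no stopping because of harm, whereas the protocol provides for such stopping of the capsules.

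**Conclusion.** The point holds in limited form. The supplementary adverse-event analysis conditions on a post-randomisation state that harm can bring about. For events that lead to stopping, it will tend to understate absolute rates and risk differences. The direction is likely but not certain. The size cannot be derived from the document: over the assumed range in Step 3, between about a third and nine tenths of the true absolute excess remains in the 80% set. Relative risk may be almost unchanged or reduced, depending on whether drug-caused events end treatment more often than background events.

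The as-randomised comparison is not biased by this, and the trial's overall assessment of harm is not shown to be understated. The point is minor to should-fix: worth correcting before database lock, but not an error that threatens the trial's conclusions.

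**What to change.** 1. State that the main adverse-event comparison covers all participants as randomised.
2. Replace the 80% adverse-event analysis with an on-treatment analysis in everyone who took at least one dose of the product in question, done separately for capsules and powder. An event that causes stopping is then counted. Use person-time as the denominator if stopping dates are recorded. The article mentions capsule counts and container weights but does not say that stopping dates are collected; if they are not, use time to the last visit on drug.
3. If an 80% set is kept, apply it per drug and state beside the table that it cannot support a conclusion of safety.

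The cost is some wording and one reprogrammed table. The trade-off is a less pure exposure contrast than in the adherent set, because people with short exposure are included.

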### Biomarkers sub-study

The analytes that will be investigated in the biomarker sub-study can be divided into three main groups; those that reflect the activity of the renin–angiotensin system or its targets, those that are markers of protein turnover and those potential novel markers of regenerative capacity that may reflect the capacity to respond to treatment. To look at the activity of the renin–angiotensin system we will measure circulating levels of ACE and renin as well as two truncated forms of angiotensin (ang(1–7) and ang(1–9)) that have been shown to alter muscle mass and are likely to be modified by an ACEi [36, 37]. There are a number of different processes through which activation of the renin–angiotensin system is thought to contribute to muscle loss, including increased inflammatory cytokine production, reduced IGF-1 production and increased myostatin production in signalling [38]. We will therefore quantify IL-6, TNF-α and myostatin. We will also quantify circulating levels of GDF-15, another member of the TGF-β family of cytokines, as it is a marker of all-cause mortality and is associated with muscle mass in patients with COPD [39] and with muscle loss following surgery [40]. The influence of specific polymorphic variation in the renin–angiotensin system will also be analysed.

To identify changes in muscle protein turnover in the absence of direct measurements, which are expensive and invasive, we will quantify pro-collagen III N-terminal peptide as a measure of new collagen synthesis [41] and levels of circulating muscle restricted miRNAs (myomiRs) that are increased in the circulation of patients with diseases associated with muscle wasting including Duchenne muscular dystrophy [42] and in chronic obstructive pulmonary disease [43].

Finally, we will examine circulating levels of a set of imprinted miRNAs that may reflect the regenerative capacity of the individual. These miRNAs include miR-518e from a paternally expressed cluster on chromosome 19 and miR-485-3p from a maternally expressed cluster on chromosome 14 which we have shown to be associated with muscle phenotype in patients with COPD [44, 45].

Univariate analyses will be conducted examining the interaction between individual baseline biomarker values and treatment effect for muscle mass and the SPPB at 12 months, and between biomarker change between baseline and 3 months and treatment effect for muscle mass and the SPPB at 12 months. In addition, multivariable analysis for baseline values including age, sex, SPPB, grip, muscle mass, albumin, creatinine, all measured biomarkers and treatment group will be conducted to examine whether baseline values or change at 3 months predicts the SPPB change and muscle mass change at 12 months.

### Sample size calculation

We have taken a deliberately conservative approach and used the minimum clinically important difference (MCID) for the SPPB to ensure we have proof of efficacy. In order to detect a MCID in the SPPB of 0.5 points (anticipated SPPB of 8 in the placebo group and 8.5 in the intervention group, SD = 2.7 points [46]) with a power of 90% at α = 0.05, and assuming a correlation between time points of 0.7 as seen from previous work [26], we would require a total of 352 participants (88 for each of the four groups). Assuming 20% dropout at 12 months (a rate of attrition consistent with that seen in previous trials of ACEi in frail older people [26]), we therefore need to recruit 440 patients. This sample size will also have 90% power to detect a 5% difference in muscle mass at 12 months, assuming a baseline value of 19 kg (SD = 2.8) for total skeletal muscle mass [47].

### Trial oversight and monitoring

Trial oversight is provided by an independent Trial Steering Committee (TSC), which meets at least every 6 months. Members include academic geriatricians with trials experience and three lay members, together with the chief investigator. The TSC reviews trial progress, approves any significant protocol changes, advises on trial conduct and approves analysis plans and dissemination plans. The TSC reports to the funder (NIHR), who has final decision-making authority for the trial. An independent Data Monitoring Committee (DMC) meets at least every 6 months; this committee comprises three independent members, chaired by an academic geriatrician with trials experience, and contains a minimum of one independent statistician. The DMC reviews trial adverse events and safety data, and makes recommendations to the TSC. Charters for conduct of the TSC and the DMC are available from the study team and from the funder. Routine management of the trial is provided by the Trial Management Group (TMG), which comprises the grant co-applicants, local site investigators, trials unit personnel from project management, data management and statistics teams, Sponsor representatives and Sponsor monitors.

Monitoring of the trial conduct at each site is provided by the Sponsor. Monitoring takes place according to a pre-specified plan, with site visits conducted according to the recruitment rate and frequency of problems identified by remote monitoring of study data. Both the Sponsor and the Clinical Trials Unit are subject to periodic audit by the UK Medicines and Healthcare products Regulatory Agency. The funder provides monitoring of overall trial progress, with additional input from the independent TSC. The final decision to publish lies with the funder (NIHR) and the Sponsor; the funder and the Sponsor have both reviewed the study design. The Sponsor will have no input into data collection, analysis and interpretation; the final report will be peer reviewed by the Funder prior to finalisation.

### Protocol amendments

Significant protocol amendments are implemented across all sites after approval by the Sponsor, the independent TSC, the funder, the ethics review board, the UK Medicines and Healthcare products Regulatory Agency and the UK Health Research Authority. The current protocol is available via the NIHR website and via the trial website (www.lacetrial.org.uk).

### Data confidentiality and post-trial care

Trial data are held separately from personal identifiers, on password-protected secure servers at the University of Dundee. Identifiable data will not be shared outside the trial team or Sponsor without written participant consent. De-identified trial data will be stored for 15 years after the end of the trial. Supplies of trial medication will not be made available to participants after the end of the trial, but both interventions are available via either prescription or via health shops. Compensation for harm suffered as a result of trial interventions or processes will be available via UK National Health Service compensation or via University of Dundee trial indemnity.

